### Study sample

Patients suitable for enrolment in the study are candidates for TKA with clinical and radiological signs of femorotibial and patellofemoral OA. Exclusion criteria are rheumatoid arthritis, history of patellar fracture, patellar ligament transposition, high tibial osteotomy (HTO), hip arthroplasty, posterior cruciate ligament (PCL) lesion and inability to read or write the Dutch language.

### Intervention

All patients will be operated using the medial parapatellar approach and will receive a posterior cruciate ligament retaining all cemented total knee prosthesis (AGC^®^ Total Knee System, Biomet, USA). Patella denervation and osteophyte resection will be performed in all patients with or without resurfacing[9, 10, 31]. In the patellar resurfacing group the patella will be resected to the appropriate size. The posterior articulating surface will be removed with the patella everted laterally. The resection will begin just below the subchondral bone at a level, which corresponds to the thickness of the patella component to be implanted. The aim of this procedure is to ensure maximum coverage of the cut surface without implant overhang. The one-peg all-polyethylene patellar prosthesis will be cemented in one stage with the tibial and femoral components. All patients will have the same postoperative rehabilitation regime.

### Main study parameter/endpoint

Primary outcome measure is the patellofemoral scoring system by Baldini et al. This tool represents patellofemoral kinematics more accurately, and may explain related patellofemoral complaints better[30]. The scoring system includes objective and subjective aspects concerning the patellofemoral joint, ranging from 0 (worst) to 100 (best)[30].

### Secondary study parameters/endpoints

Knee function will be assessed by means of two scoring systems: the Knee Society clinical rating system (KSS) and the Knee injury and Osteoarthritis Outcome Score (KOOS). The KSS is subdivided into a knee score that rates only aspects of the knee joint itself, such as range of motion and stability, and a functional score that rates the patient’s ability to walk and climb stairs[32].The KOOS is developed as an instrument to assess patients’ opinion about their knee and associated problems[33, 34]. The KOOS consists of 5 subscales; pain, other symptoms, function in daily living, function in sport and recreation, and knee-related quality of life, with scores ranging from 0 (worst) to 100 (best).

Component loosening, wear, and patellofemoral problems including fracture or loosening of resurfaced patellae, subluxation and wear of non-resurfaced patellae will be assessed on conventional weight-bearing radiographs and views according to Baldini[35]. The view according to Baldini is a dynamic weight-bearing axial radiographic view of the patellofemoral joint with the patient standing in a semi-squatting position with knees in 45 degrees of flexion (Figure 1)[29].

**Figure 1 Fig1:**
[figure not shown]
**View according to Baldini**[29]**.**

### Randomization

Patients who meet the inclusion criteria will be informed about the study by their orthopaedic surgeon at the Department of Orthopaedics of Martini Hospital Groningen. They will be informed about the treatment and the risk of complications according to the Dutch Medical Treatment Contracts Act. After consenting to participate, patients will be randomly assigned to one of the two regimens in a 1:1 ratio (Figure 2). The schedule for randomisation will be randomly generated using a computer before initiation of the study. To conceal the outcomes of the randomization, the allocation numbers will be put into concealed, opaque envelopes. An independent researcher will prepare the envelopes. Following informed consent, a randomization envelope will be opened. The randomisation allocation will not be notified to either the patient or the independent researcher, as both patient and investigator will be blinded to the outcome of the randomization.

**Figure 2 Fig2:**
[figure not shown]
**Flowchart of patient inclusion.**

### Data collection methods

Preoperatively as well as at six weeks, and six, 12,18 and 24 months postoperatively patient assessments will be performed. Age, gender, body mass index (BMI), severity of OA, will be recorded preoperatively. Perioperative complications will be registered. Primary and secondary outcome measurements will be obtained at all time points by an independent investigator (Table 1).

**Table 1 Tab1:** **Data (time) management**

Follow-up	X-rays	Documentation
Day 0	Knee AP and Lateral	Basic characteristics (incl. BMI)
	Baldini	KSS/Baldini/KOOS
		Physical examination
		Informed consent
	Randomisation	
**Operation**		Standardised report
Day 1- Day 5	Knee AP and lateral	Wound check
Week 6	Knee AP and lateral	Wound check, KSS/Baldini/KOOS
	Baldini	
Month 6		KSS/Baldini/KOOS
		Physical examination
Month 12	Knee AP and lateral	KSS/Baldini/KOOS
	Baldini	Physical examination
Month 18	Knee AP and lateral	KSS/Baldini/KOOS
	Baldini	Physical examination
Month 24	Knee AP and lateral	KSS/Baldini/KOOS
	Baldini	Physical examination

### Sample size calculation

Using the patellofemoral scoring system by Baldini et al.[30], the sample size is based on a mean difference of 10 points between both groups at 2-years follow-up. To detect this difference of 10 points with a standard deviation of 8 points, alpha of 5% and a power of 90%, a sample size of 18 patients in each study group is required. To compensate for potential drop-out and loss to follow-up, a total of 50 patients will be included in the study.

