### Statistical analysis

All statistical analyses will be computed using SPSS (IBM SPSS, Inc., Version 20.0, 2011). For the clinical parameters, t-tests will be used for continuous variables or the Mann–Whitney U-test when the variables are not normally distributed. A Chi-square test will be used for dichotomous variables. To assess differences in the results of the Baldini score and the KOOS over time between the two study groups, generalised estimating equations (GEE) analyses will be conducted. Longitudinal data are characterised by repeated observations of the same subjects. GEE analysis was developed to correct for repeated outcomes within the same subject[36]. With a GEE analysis, adjustments for the effect of differences in patient characteristics on the outcome variables can also be made by including these variables as covariates. Both an intention-to-treat analysis as a per-protocol analysis will be performed.

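### The 18 patients per group do not follow from the printed inputs: a two-sided t-test needs 15 for 90% power, and 18 gives 95%

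*Protocol article*

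**What the plan says.** In the protocol article, Sample size calculation, "the sample size is based on a mean difference of 10 points between both groups at 2-years follow-up", measured on the 0 to 100 Baldini score. The remaining inputs and the result follow in one sentence: "standard deviation of 8 points, alpha of 5% and a power of 90%, a sample size of 18 patients in each study group". The next sentence raises the total: "To compensate for potential drop-out and loss to follow-up, a total of 50 patients will be included in the study". The section does not say whether alpha is one- or two-sided, which test underlies the calculation, or what loss rate is assumed.

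Under Randomization, "patients will be randomly assigned to one of the two regimens in a 1:1 ratio". Under Statistical analysis, "t-tests will be used for continuous variables", with the Mann-Whitney U-test as the alternative when the data are not normal, and generalised estimating equations for the Baldini score and the KOOS over time.

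**The concern.** The article prints every number that a standard two-group calculation needs (difference, standard deviation, alpha, power) together with the answer, so the answer can be checked. A standardised difference of 10/8 = 1.25 is large, and 18 per group looks too many for 90% power.

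This is the only justification given for the size of a surgical trial. If number and power do not match, the reader cannot tell what was assumed. Someone planning a later trial with this score might reuse a standard deviation of 8 when the calculation had really used a larger one. A reader judging a null result would also take 10 points as the difference detectable with 90% power at 18 per group, when on the printed standard deviation that difference is 8.9 points.

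**Working it through.** **Inputs.** From Sample size calculation: difference 10, standard deviation 8, alpha 5%, power 90%, stated result 18 per group. From Randomization: 1:1 allocation. Assumed: two-sided alpha, since the article does not say; one-sided is checked below. Test: two-sample t-test, as named first under Statistical analysis.

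**Step 1. Normal approximation.**
n per group = 2 × (z for alpha + z for power)² × (SD/difference)²
= 2 × (1.960 + 1.2816)² × (8/10)² = 13.45, so 14 per group.

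**Step 2. Exact t-test power.** The noncentral t distribution has 2n − 2 degrees of freedom and noncentrality 1.25 × √(n/2). At n = 18 the noncentrality is 1.25 × 3 = 3.75.

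| n per group | Power, two-sided 5% |
|---|---|
| 14 | 88.9% |
| 15 | 91.0% |
| 18 | 95.4% |
| 25 | 99.1% |

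The smallest n that reaches 90% is 15, or 30 in total against the stated 36. The plan's 18 is not reproduced. It is the smallest n that reaches 95%.

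**Step 3. Could another reading of the printed inputs give 18?**
- *One-sided alpha of 5%:* 11 per group by normal approximation, 12 by t-test. This is further from 18.
- *Drop-out already included:* 15/0.85 = 17.6 would round up to 18, but the article presents 18 per group as the number required and then adds the allowance to go from 36 to 50.
- *Repeated measures:* the calculation is framed as a between-group difference at two years and gives no correlation. Using the earlier visits would not normally raise the requirement.

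**Step 4. What does give 18?**
- *95% power with a standard deviation of 8:* 18 by exact t-test. This contradicts the printed power.
- *Two-sided alpha of 2.5%:* 18 (91.4% power). This contradicts the printed alpha.
- *A standard deviation of about 8.9:* 18 by exact t-test. This contradicts the printed 8. A standard deviation of 9.0 does not quite fit: 18 per group then gives 89.9%, and 19 are needed.
- *A rank-test inflation of the t-test figure:* 15/0.864 = 17.4, rounded up to 18, where 0.864 is the minimum efficiency of the Mann-Whitney test relative to the t-test. A flat 15% addition also works: 15 × 1.15 = 17.25, so 18. Both keep every printed input, but neither is mentioned. With the efficiency for normal data the result is 15/0.955 = 15.7, so 16. Putting 0.864 inside the power calculation gives 17 (90.4%).

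**Step 5. Loss that 50 can absorb.** 1 − 36/50 = 28%, or 14 patients, if losses fall evenly between the groups.

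**The case against.** The strongest objection is that every printed input may be correct. The Mann-Whitney test is named as the fallback, and inflating 15 for it by the worst-case efficiency, or by 15%, gives exactly 18. On that account nothing is misreported and only the method is unnamed, which a condensed article might leave to the full protocol. This stands in part. It rules out the stronger inference a reader might draw, that the stated power or standard deviation must be wrong, because the article does not allow that conclusion. It does not remove the discrepancy. The article describes its calculation by a mean difference and a standard deviation, names no inflation, and presents 18 as what those inputs require.

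Two further inferences are tempting and also fail. One is that the planning standard deviation was really 9. Nothing in the article gives that figure, and 9 does not reach 90% at 18 per group by exact t-test. The other is that the loss allowance is misdescribed. The article states no loss rate, so there is none to contradict; the 28% is derived here.

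It is also fair to say that the practical effect is small. The discrepancy runs in the safe direction. Even with a standard deviation of 9, 25 per group would give 97.1% power.

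**Conclusion.** The point holds as a reporting and arithmetic correction. With the printed inputs and a two-sided two-sample t-test, 90% power needs 15 per group, not 18, and 18 gives 95.4%. The gap is 3 patients per group (6 in total) or 5.4 percentage points of power, which is more than rounding. Confidence is high that the printed figures do not agree under a plain t-test. The article does not show which input or unnamed step accounts for the difference.

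The conclusion assumes two-sided alpha, equal groups, a common standard deviation and a comparison at 24 months. One-sided alpha would widen the gap. On the article's own assumptions the trial is not underpowered: 18 evaluable per group exceed the 90% target, and 25 per group without loss give 99.1%.

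**What to change.** Restate the calculation so that its figures agree. If the printed inputs are the ones intended, for example: 18 evaluable patients per group give 95% power with a two-sided 5% t-test to detect 10 points with a standard deviation of 8; 15 per group would be enough for 90% (exact power 91.0%). If another standard deviation or a non-parametric inflation was actually used, state it, and check that it returns 18 by the named method. In either case name the test and the sidedness.

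Keep the total of 50 and add that it leaves 36 evaluable patients after up to 28% loss. The cost is one corrected sentence; enrolment, follow-up and analysis do not change.

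### Enrolling 50 patients replaces numbers but not comparability: the named t-tests and loosely specified GEE could understate the 24-month Baldini difference if poor scorers drop out more in one arm

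*Protocol article*

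**What the plan says.** All references are to the Protocol article.

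- **Background** sets the hypothesis as a between-group difference in Baldini score 24 months after surgery.
- **Sample size calculation** plans for "a mean difference of 10 points between both groups at 2-years follow-up", with SD 8, alpha 5% and power 90%, and concludes that "a sample size of 18 patients in each study group is required". It then says: "To compensate for potential drop-out and loss to follow-up, a total of 50 patients will be included in the study". No drop-out rate is printed.
- **Randomization** allocates patients 1:1, so 25 per arm.
- **Data collection methods** and **Table 1** schedule the Baldini score preoperatively, at 6 weeks, and at 6, 12, 18 and 24 months.
- **Statistical analysis** names t-tests (or Mann-Whitney) for clinical parameters, and GEE for the Baldini score and KOOS over time. Its reason for GEE is that "GEE analysis was developed to correct for repeated outcomes within the same subject". It names no working correlation and no weighting. It adds: "Both an intention-to-treat analysis as a per-protocol analysis will be performed".

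**The concern.** The only provision for loss is a larger intake. That protects power but not the point estimate.

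A 24-month t-test compares the patients still attending. So does GEE with an independence working correlation and group-by-visit effects: its 24-month estimate is the difference in means among those observed. Neither uses a departed patient's earlier scores to correct the 24-month comparison.

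The trial's own premise makes unequal loss plausible. Background cites a 14% absolute reduction in anterior knee pain with resurfacing, and the trial expects a higher Baldini score in the resurfaced arm. If low scores prompt patients to leave, even one common rule removes more patients from the non-resurfaced arm. Those who stay then look better than the group that was randomised, and the difference shrinks. A result labelled intention-to-treat would in fact compare selected stayers.

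**Working it through.** **1. The plan's own figures.** Inputs from Sample size calculation: difference 10, SD 8, alpha 5% (two-sided assumed), power 90%.

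- n per group = 2 × (1.96 + 1.2816)² × 8²/10² = 2 × 10.51 × 0.64 = 13.4, so 14. The exact t calculation gives 15.
- The stated 18 is therefore not the direct result of the printed inputs. It is conservative and does not affect the argument about bias.
- Implied allowance: 1 - (2 × 18)/50 = 28%, or 25 - 18 = 7 patients per arm.

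**2. Size of the possible bias.** The article gives no drop-out model or within-patient correlation, so the following are assumptions:

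- five postoperative visits, SD 8, true difference 10 at every visit;
- correlation exchangeable (0.3 to 0.7) or first-order autoregressive (0.5 to 0.85);
- 28% overall drop-out without return, driven by the previous score with a log-odds slope of 2 per SD;
- large simulated samples, so that bias is visible apart from chance.

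Estimated 24-month difference (truth 10) when the same rule acts in both arms:

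| Correlation | Drop-out, non-resurfaced / resurfaced | t-test or independence GEE | Exchangeable GEE | Unstructured GEE |
|---|---|---|---|---|
| Exchangeable 0.3 | 46% / 10% | 8.73 | 9.92 | 9.94 |
| Exchangeable 0.5 | 45% / 11% | 8.07 | 9.90 | 9.91 |
| Exchangeable 0.7 | 44% / 12% | 7.45 | 9.84 | 9.84 |
| Autoregressive 0.5 | 45% / 11% | 8.97 | 10.23 | 9.87 |
| Autoregressive 0.7 | 45% / 11% | 8.39 | 10.31 | 9.92 |
| Autoregressive 0.85 | 44% / 12% | 7.63 | 10.14 | 9.83 |

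**3. Other settings.**

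- *Weaker dependence included (slope 1 or 2 per SD):* the observed-patient estimate is 7.5 to 9.5 in one run and 7.4 to 9.7 in another. The shortfall is roughly 10 - 9.7 = 0.3 to 10 - 7.5 = 2.5 points.
- *Overall loss of 10% instead of 28%:* 8.9 to 10.0.
- *Likelihood-equivalent fit to all visits with the data's covariance:* 9.68 to 10.40. With 4,000 per arm, the standard error of a complete-data difference is already 8 × √(2/4000) = 0.18, so this is compatible with 10.
- *Drop-out unrelated to scores:* every method gives about 10.
- *No true effect, same rule in both arms:* every method gives about 0.
- *Only non-resurfaced patients leave (56% of that arm), an extreme case:* the observed-patient estimate is 5.5 to 8.3 when the truth is 10, and -1.6 to -4.5 when the truth is 0. Exchangeable or unstructured GEE stays within 9.9 to 10.6 and -0.1 to 0.65.

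**4. Effect on power.** With 18 per group, power ≈ Φ(d/8 × √(18/2) - 1.96).

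- d = 10: Φ(3.75 - 1.96) = 96%.
- d = 7.5: Φ(2.81 - 1.96) = 80%.

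**The case against.** **The article is silent rather than wrong.** It does not choose independence, does not rule out weighting or imputation, and may leave both to an analysis plan that is not shown. This stands: the absence of a missing-data policy is not the point here. What remains is that the methods it does name carry no general guarantee when drop-out depends on scores. An analysis plan that simply carried out this section as written could produce the biased estimate.

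**GEE need not be biased.** A reader might infer that any GEE here is unbiased only when drop-out ignores earlier scores. The results above do not support that: with an exchangeable or unstructured working correlation the bias was small.

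**The t-test is not named as the primary Baldini analysis.** Correct. The section gives t-tests for clinical parameters and assigns Baldini over time to GEE. It does not say which supplies the 24-month comparison, so the completer t-test is a possible reading, not a stated choice.

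**28% is headroom, and the steep scenarios exceed it in one arm.** Also correct. Losing 45% of 25 leaves about 14, below the required 18, although the two arms together still total about 36. The article does not forecast 28% loss.

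**The mechanism is assumed.** Nothing in the article says that patients in pain stop attending; they might attend more. Patients are also meant to be blinded to allocation.

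**Small-sample behaviour is untested.** The simulations are large. An unstructured covariance over six visits has 6 × 7/2 = 21 parameters for 50 patients, which is why the fix needs a fallback.

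**Conclusion.** The point holds in conditional form. The allowance for 28% loss protects the number of patients, not the comparison between arms. The methods named are guaranteed unbiased for the 24-month difference only if drop-out is unrelated to observed scores. If poor scorers leave more often and the arms are affected unequally, a completer t-test or independence-working GEE could understate a true 10-point difference by roughly 0.3 to 2.5 points at 28% loss, and by at most about 1.1 points (10 - 8.9) at 10% loss. These sizes rest on the assumed correlations and score-driven drop-out, none of which is in the article.

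A reader might go further and say that drop-out will bias the primary result. The documents do not support that. They fix neither the working correlation nor a completer analysis, they predict no drop-out rate, and bias requires score-related loss that differs between arms. Because the choice left open separates a material bias from a negligible one, and the needed visits are already scheduled, the wording should be tightened. Confidence is medium.

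**What to change.** In the Statistical analysis section, state the following:

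- The intention-to-treat estimate of the 24-month Baldini difference comes from a likelihood-based repeated-measures model with group, visit and group-by-visit terms, using all randomised patients and all observed visits. The covariance is unstructured, with a named simpler structure as fallback if the model does not converge with 50 patients.
- If GEE is kept, it uses a non-independence working correlation, preferably after multiple imputation of missing scores from earlier visits.
- The primary estimate is not a t-test on 24-month completers.
- Drop-out is reported by arm, with reasons.

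The cost is analysis wording, a record of the reason for each drop-out, and slightly more analysis work. No visits or patients are added. The trade-off is reliance on a model for the missing visits: it covers drop-out that depends on earlier observed scores, not drop-out that depends on scores never seen.

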### Statistical analysis

All statistical analyses will be computed using SPSS (IBM SPSS, Inc., Version 20.0, 2011). For the clinical parameters, t-tests will be used for continuous variables or the Mann–Whitney U-test when the variables are not normally distributed. A Chi-square test will be used for dichotomous variables. To assess differences in the results of the Baldini score and the KOOS over time between the two study groups, generalised estimating equations (GEE) analyses will be conducted. Longitudinal data are characterised by repeated observations of the same subjects. GEE analysis was developed to correct for repeated outcomes within the same subject[36]. With a GEE analysis, adjustments for the effect of differences in patient characteristics on the outcome variables can also be made by including these variables as covariates. Both an intention-to-treat analysis as a per-protocol analysis will be performed.

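### The KSS is collected at the same visits as the Baldini score and KOOS but is not named in the longitudinal analysis, and no visit or use of its preoperative value is stated

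*Protocol article*

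**What the plan says.** All references are to the protocol article.

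- **Secondary study parameters/endpoints** names two scoring systems for knee function, the KSS and the KOOS. The KSS yields two scores: "The KSS is subdivided into a knee score that rates only aspects of the knee joint itself", and a separate functional score covers walking and stairs.
- **Data collection methods** sets the schedule: "Preoperatively as well as at six weeks, and six, 12,18 and 24 months postoperatively patient assessments will be performed". It adds: "Primary and secondary outcome measurements will be obtained at all time points".
- **Table 1** lists the three instruments together at day 0, week 6 and months 6, 12, 18 and 24. The week 6 entry, for example, reads "Wound check, KSS/Baldini/KOOS".
- **Statistical analysis** introduces GEE with the words "To assess differences in the results of the Baldini score and the KOOS over time between the two study groups". Its reason is that the same patients are observed repeatedly. It says that covariates describing patient characteristics can be added.
- The only other rule in that section for continuous data is that "t-tests will be used for continuous variables or the Mann–Whitney U-test when the variables are not normally distributed". This rule is for the clinical parameters, a term the section does not define.

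**The concern.** Three instruments share one schedule, and two of them are assigned to a longitudinal model. The third is not mentioned, and no reason is given. The article's vocabulary suggests where it falls: the KSS is called a clinical rating system, and the Discussion gives it as an example of a clinical outcome measure, in contrast to the patient-reported KOOS. On that reading the KSS goes to the t-test or Mann–Whitney rule. On any other reading it has no stated analysis.

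Two things are at stake for a secondary outcome. An unadjusted two-sample test at one visit ignores a preoperative value that has already been collected, and so gives up precision in a trial of 50 patients. And with six measurement times and no visit named, the reader cannot tell which KSS comparison is the planned one.

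**Working it through.** **Plan's own figure.** The article gives no figure for the KSS. Its one calculation, 18 per group, concerns the Baldini score and does not enter here.

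**Step 1: place the KSS in the plan.**

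| | Baldini | KOOS | KSS knee and function |
|---|---|---|---|
| Preoperative value | yes | yes | yes |
| 6 weeks; 6, 12, 18, 24 months | yes | yes | yes |
| Named in the GEE sentence | yes | yes | no |
| Stated visit for the analysis | 24 months (hypothesis and sample size) | none | none |
| Stated adjustment for the preoperative score | none | none | none |

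The third row is specific to the KSS. The last row is not: the GEE text allows patient characteristics as covariates but does not commit to the preoperative score for any outcome.

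**Step 2: what the preoperative value is worth.** Take n patients per arm, follow-up SD σ, and correlation r between the preoperative and follow-up score. The variance of the group difference at one visit is:

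- follow-up values only: 2σ²/n
- adjusted for the preoperative value: about 2σ²(1 − r²)/n
- change scores, with equal SD at both times: 2σ² × 2(1 − r)/n

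The article does not give r, so the values below are assumptions.

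| r | Adjusted ÷ follow-up only | Variance saved | CI width factor √(1 − r²) | Change score ÷ follow-up only, 2(1 − r) |
|---|---|---|---|---|
| 0.3 | 0.91 | 9% | 0.95 | 1.40 |
| 0.5 | 0.75 | 25% | 0.87 | 1.00 |
| 0.6 | 0.64 | 36% | 0.80 | 0.80 |

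A t-test on change scores would use the preoperative value. At these correlations it is never better than covariate adjustment, and at r = 0.3 it is worse than ignoring baseline.

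If data are complete and the model has a free allocation-by-visit term, the repeated measurements alone add nothing to the 24-month contrast. The gain at that visit comes from the baseline covariate. The model also keeps patients with some missing visits in the analysis and describes the course over time.

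**Step 3: a conditional check on multiplicity.** Suppose each of the five postoperative visits were tested at 0.05 and any significant visit counted. The article does not say this. With independent visits the chance of at least one false positive is 1 − 0.95⁵ = 22.6% for one KSS score. With correlated visits (20,000 simulated null trials, exchangeable correlation assumed):

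| Between-visit correlation | 18 per arm | 25 per arm | Mean of the two |
|---|---|---|---|
| 0.3 | 21.7% | 21.1% | 21.4% |
| 0.5 | 18.5% | 18.7% | 18.6% |
| 0.7 | 15.5% | 14.4% | 15.0% |

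This is roughly 15 to 21% for one score. Each single test keeps its 5% level (simulated per-visit rates were 4.8 to 5.2%).

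**The case against.** The strongest case on the other side is that the article is silent here rather than wrong. It is a condensed account, the method for a secondary score is often left to the analysis plan, and the GEE sentence does not say that it excludes other outcomes. Much of this stands, and it rules out four stronger readings.

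- **That the KSS will be tested at every visit, with an inflated false-positive rate.** The article does not say so. The hypothesis and sample size are both set at 24 months, so a single 24-month KSS test is at least as natural a reading, and it carries no inflation across visits. The percentages in step 3 belong to a decision rule that the plan does not state.
- **That the KSS analysis discards baseline while the other scores use it.** A t-test on change scores is not excluded, and the GEE text does not commit to the preoperative score either. Naming the KSS in that sentence would not by itself bring baseline in.
- **That GEE would cure the multiplicity.** It would not. GEE contrasts read visit by visit, or across the five KOOS subscales, raise the same issue. Fixing one contrast is what removes it across visits.
- **That the Discussion plans to compare effects between instruments, so all three need the same method.** It calls the Baldini score complementary because the other two do not focus on the patellofemoral joint. That concerns instrument content; no comparison of treatment effects across scores is planned.

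What the objection does not answer is the explicit list. The section gives a reason for GEE that fits the KSS exactly, then names two of the three instruments that meet it.

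**Conclusion.** The point holds in limited form. Both KSS scores share the full schedule of the Baldini score and KOOS but are not named in the longitudinal analysis. They are most naturally left to unadjusted two-sample tests, with no stated visit and no stated use of the preoperative KSS or the repeated measurements.

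The gain on offer is precision: about 9%, 25% or 36% less variance for assumed r of 0.3, 0.5 or 0.6, compared with a test on follow-up values alone. The 15 to 21% familywise rate would apply only if all five postoperative visits were tested separately, under assumed between-visit correlations of 0.3 to 0.7. A reader might infer such testing, but the article does not state it.

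The KSS is secondary. The primary outcome, its sample size and the 24-month hypothesis are untouched. This is a minor improvement.

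**What to change.** In the Statistical analysis section, or in the analysis plan if that is where the detail sits:

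1. Name the KSS knee score and KSS function score in the GEE sentence beside the Baldini score and the KOOS subscales.
2. For every one of these scores, model the five postoperative values with allocation, visit and allocation-by-visit, and include the preoperative value of the same score as a covariate. This is new for the Baldini score and KOOS as well.
3. State that the KSS comparison is the 24-month group contrast with its 95% CI, and that the other visits are descriptive.
4. Keep the t-test, Mann–Whitney and chi-square tests for variables measured once.

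The cost is one sentence on the KSS, a covariate added to models already planned, and two extra model runs. All the data are already scheduled for collection.
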